# Efficacy of smartphone-based virtual reality relaxation in providing comfort to patients with cancer undergoing chemotherapy in oncology outpatient setting in Indonesia: protocol for a randomised controlled trial

**DOI:** 10.1136/bmjopen-2023-074506

**Published:** 2023-07-25

**Keywords:** Virtual Reality, CHEMOTHERAPY, Nursing Care, Adult palliative care

## Abstract

**Introduction:**

Patients with cancer undergoing chemotherapy experience various physical and psychological problems and discomfort. Virtual reality (VR) can be used in technology-based non-pharmacological therapy that can serve as a potential distractor in the symptom management of patients with cancer undergoing chemotherapy. We propose a smartphone-based virtual reality relaxation (S-VR) technique as a complementary modality to provide comfort to patients with cancer, and we will evaluate its effect on patients with cancer undergoing chemotherapy.

**Methods and analysis:**

We will recruit 80 patients from the One Day Chemotherapy ‘Tulip’ Center of [name] Hospital, Yogyakarta, Indonesia. This will be a two-arm parallel randomised controlled trial, with a 1:1 allocation and the primary outcome assessor blinded. This study will be divided into two groups: (1) an intervention group, with participants receiving 360° panoramic video content and music relaxation intervention through a VR device (head-mounted display) placed on their head during chemotherapy for ±10 min plus standard care and (2) a control group, with participants receiving guided imagery relaxation therapy in the form of a leaflet plus standard care. We will measure the outcomes after one chemotherapy cycle for each participant. The primary outcome is the effectiveness of the S-VR in improving the comfort of patients. The secondary outcome is the effect of the S-VR on the patients’ symptom management self-efficacy, pain, anxiety, blood pressure (systolic blood pressure and diastolic blood pressure) and pulse rate.

**Ethics and dissemination:**

This study was approved by the Medical and Health Research Ethics Committee of the Faculty of Medicine, Public Health and Nursing of Universitas Gadjah Mada—[name] Hospital, Yogyakarta, Institutional Review Board (approval number: KE/FK/0301/EC/2023). Written informed consent will be obtained from all participants who enrol in the study. Dissemination will be conducted through peer-reviewed publications and conference presentations.

**Trial registration number:**

NCT05756465.

STRENGTHS AND LIMITATIONS OF THIS STUDYIn addition to patient-reported outcomes, the present randomised controlled trial will assess patients’ bio-parameters, such as blood pressure and heart rate, as well as cybersickness symptom evaluation due to the virtual reality (VR) device.We will increase the sample size and make it larger than minimum sample size to increase statistical power.The principal objective of this study was to enhance patient comfort during the brief duration of chemotherapy within the chemotherapy room.We will not assess the patients’ pre-existing psychological conditions, which may affect their response to VR intervention.This study conducts in a single institution, which may limit the generalisability of the findings to other settings and populations.

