## Introduction

The cancer incidence in Indonesia (136.2/100 000 population) is the 8th highest in Southeast Asia and 23rd highest in Asia.^1^ According to Basic Health Surveillance (Riskesdas),^2^ the prevalence of cancer in Indonesia increased from 1.4 in 2013 to 1.49 in 2018. Of the total of 396 914 cancer cases in Indonesia in 2020, the top three most common cancer types were breast cancer (65 858 cases; 16.6%), cervical cancer (36 633 cases; 9.2%) and lung cancer (21 392 cases; 8.8%).^3^ The region with the highest prevalence of cancer is the Special Region of Yogyakarta (DIY) Province (4.86/1000 population), and 23% of the patients with cancer in this region receive chemotherapy, which is the second-most-common cancer management strategy after surgery.^2^

Patients undergoing chemotherapy experience various adverse effects.^4^ Moreover, they may experience physical and psychological discomfort caused by the treatment drugs, invasive procedures and chemotherapy environments. In general, 86% of patients with cancer experience pain, nausea, vomiting, mucositis, diarrhoea and alopecia.^5 6^ Other side effects include psychological problems, such as anxiety, feelings of hopelessness, depression, anger, fear, vulnerability and a sense of loss of control.^7^ Management of the side effects of chemotherapy by using drugs is not fully effective and may cause other side effects, which can cause further patient discomfort.^8 9^

Comfort is defined as a lack of pain, distress, worry and uneasiness, and it is one of the most crucial factors in holistic nursing care.^10 11^ Focusing on patients’ biophysiological aspects (eg, symptom management) as well as psychospiritual, environmental and sociocultural aspects related to healing is crucial for maintaining their well-being.^12^ Kolcaba explained that in addition to providing basic care to patients, nurses must provide special and unique nursing care to each patient to increase patient comfort.^13 14^ Patients with cancer require physical, social and spiritual support and a comfortable environment to have a sense of life meaning.^12 15 16^ Meeting the comfort needs of patients with cancer positively affects the patients’ satisfaction with the services they receive, their treatment adherence and their overall quality of life.^11 17^

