## Methods and analysis

### Design

This study is a two-arm parallel randomised controlled trial with a 1:1 allocation. The study will divide the patients into two groups: the intervention group, in which the patients will receive S-VR therapy through a VR device (head-mounted display) mounted on the patients’ heads during chemotherapy plus standard care (daily routine care in administration of chemotherapy drugs), and the control group, in which the patients will receive standard care and guided imagery therapy with leaflets containing instructions for techniques for relaxing through image visualisation. The group allocation will be implemented using the envelope concealment method, and the outcome assessor will be blinded to the group allocation during data collection. The protocol has been designed in accordance with the Standard Protocol Items: Recommendations for Interventional Trials and its checklist.^30 31^
Figure 1 presents the modified Consolidated Standards of Reporting Trials^32^ flow diagram.^32^

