### Sample size calculation

The sample size was calculated using free-to use software, namely G*Power for Windows V.3.1.9.6.^33^ The effect size is 0.81, type 1 error (α)=5% (two-tailed), power (1−β) 90% and the allocation ratio between the groups is 1:1. The effect size was set with reference to previous studies with similar outcomes.^9^ According to the G*Power calculation, the study sample size should be 34 per group. With consideration of an expected dropout rate of 15%, the sample size was increased to 40 per group.

The participant dropout criteria are as follows:

The patient being unwilling to continue the sequence of the study process (lost to follow-up).The patients experiencing drug extravasation incidents or severe side effects during chemotherapy.

The consecutive sampling technique will be applied. This non-probability sampling method involves recruiting all individuals from the accessible population during a given time interval or for a specific sample size. Patients with cancer who have scheduled chemotherapy and meet the requirements of the data collection time will be asked to participate in the study.

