Anxiety is measured using the Visual Analogue Scale for Anxiety (VAS-A) in the form of a horizontal line with a scale of 100 mm or 10 cm, with the left by the words ‘not at all anxious’ and on the right by ‘extremely anxious’.^36 37^ VAS-A has a sensitivity of 76.8%, specifications of 64.9% and internal reliability consistency (Cronbach’s α ≥0.7).^36 37^

Pain is measured using the Numerical Rating Scale (NRS). The NRS consists of numerical scale; from 0 to 100 (101-point scale), 0 to 10 (11-point scale) or 1 to 10 (10-point scale). This study will use a 0–10 NRS due to it provides more sufficient sensitivity to measure pain in most patients with cancer.^38^ The NRS has been declared valid and reliable for subjective measurement of cancer pain, both due to adverse effects of cytotoxic agents, cancer treatment procedures (surgery, radiotherapy and chemotherapy) and the malignancy of the cancer itself.^39^

Pulse rate and blood pressure (systolic and diastolic pressure) are measured using an automatic digital sphygmomanometer. According to American Heart Association, the regular resting heart rate for adults is 60–100 beats per minute, and systolic blood pressure is above 90 mm Hg and less than 120 mm Hg, with a diastolic pressure between 60 mm Hg and less than 80 mm Hg.^40^

Comfort and self-efficacy for symptom management will be measured at two time points: at baseline (before chemotherapy premedication) and post-test (after the chemotherapy session is completed). Anxiety, pain and vital signs (pulse rate and blood pressure) will be measured at five time points: thrice at pretest (baseline data collection, before the installation of intravenous access and before administration of VR intervention) and twice at post-test (immediately after intervention and after the chemotherapy session is completed). The timeline of the data collection and measurement is presented in table 2.

**Table 2 T2:** Timeline of data collection and measurements

Assessment/measurement instrument	Study period				
	T0	T1	T2	T3	T4
Demographic variables	**X**				
Clinical characteristics	**X**				
SGCQ	**X**				**X**
SE-CSSMS	**X**				**X**
VAS-A	**X**	**X**	**X**	**X**	**X**
NPRS	**X**	**X**	**X**	**X**	**X**
Blood pressure	**X**	**X**	**X**	**X**	**X**
Pulse rate	**X**	**X**	**X**	**X**	**X**

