### Data analysis

The collected data will be processed using IBM SPSS statistical software V.23 for Windows through editing, coding and data entry processes. The statistician will be blinded to the study outcomes and will conduct analyses on the basis of the labelling of the groups. For the treatment group, the demographic and clinical variables recorded at enrolment will be tabulated. The descriptive statistics will be presented as numbers, means, SDs, medians, minimums and maximums. Homogeneity and normality tests will be conducted before the bivariate analysis test. A homogeneity test for categorical data (age, sex, education level, marital status, occupation, income, the presence of a family member or caregiver during chemotherapy, type of cancer, stage of cancer, duration of cancer diagnosis, chemotherapy cycle and ECOG Scores) will be performed using the χ^2^ test or Fisher’s test, whereas a homogeneity test for numerical data (height and weight) will be performed using Levene’s test if the data are normally distributed and using the Mann-Whitney U test if the data are not normally distributed. Both groups will be considered to be homogeneous if p>0.05. Bivariate analysis will be used to determine the differences in the mean scores for comfort level and symptom management self-efficacy before and after treatment in the intervention and control groups. If the data distribution is normal, we will use a paired t-test and independent t-test. However, if the data distribution is not normal, the non-parametric Wilcoxon and Mann-Whitney U tests will be used if significant differences are identified (p<0.05). For anxiety, pain and vital-sign (blood pressure and pulse rate) outcome measurement analysis, General Linear Model-Repeated Measure (GLM-RM) statistics will be used. The GLM-RM is a statistical test used for the comparative analysis of two unpaired numerical data groups with more than two measurements and is applied when the effect of a treatment or intervention is measured at different time points. If the data are not normally distributed, the repeated Mann-Whitney alternative test with Bonferroni correction will be used. The present study will use statistical method to adjust for potentially confounding effects of the S-VR intervention on the patient’s outcomes. These confounders include age, gender, education, cancer stage, chemotherapy cycle, assistance during chemotherapy and comorbidities. Multivariate model can handle identified confounders and minimise the bias effect of the intervention.^45^ Linear regression analysis will be applied by using the enter method. Adjustment by using this analysis can clarify that how much the confounders in the model distort the intervention and outcome.^46^

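### The adjusted comfort regression leaves out baseline anxiety and baseline pain, which are measured in every patient and are likely predictors of comfort: a minor, cheap gain in precision forgone

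*Protocol article*

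**What the plan says.** In the strengths and limitations box, the article states: "We will not assess the patients’ pre-existing psychological conditions, which may affect their response to VR intervention".

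Under Outcomes, the measurement schedule reads: "Anxiety, pain and vital signs (pulse rate and blood pressure) will be measured at five time points: thrice at pretest". Table 2 marks VAS-A and NPRS at T0. Patient recruitment places the pretest before the envelope is opened, so the T0 values are unaffected by knowledge of the allocation.

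The Introduction sets out the construct behind the primary outcome: "Comfort is defined as a lack of pain, distress, worry and uneasiness".

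Data analysis commits to a linear regression with all covariates entered, for the patient's outcomes in general, and names the adjustment factors: "These confounders include age, gender, education, cancer stage, chemotherapy cycle, assistance during chemotherapy and comorbidities". T0 anxiety and T0 pain are not among them. Nor is T0 comfort (SGCQ). ECOG is collected, but in that section it appears only in the between-group homogeneity tests.

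**The concern.** If comfort is understood as freedom from pain and worry, a patient's anxiety and pain on arrival should help to predict comfort after the session. Both are recorded in everyone at no extra cost. An adjustment set that spends its degrees of freedom on age, gender, education and similar factors, and omits the two measured variables closest to the outcome's definition, looks poorly chosen.

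Two things are at stake. One is precision in a trial of about 68 to 80 patients. The other is that a chance difference between the arms in T0 anxiety or pain, which simple unstratified randomisation allows, is not corrected by the listed model. Timing matters as well: adding these covariates after an imbalance has been seen would be a post hoc choice.

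**Working it through.** **Inputs from the article (Sample size calculation).** "The effect size is 0.81"; two-sided alpha 0.05; power 90%; 1:1 allocation; 34 per group, raised to 40 for 15% dropout.

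**The plan's own figure.** The two-sample t-test with the noncentral t distribution gives power 0.8998 at 33 per group and 0.9084 at 34. So 34 is reproduced, and 34/0.85 = 40.

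**Assumptions, because the article gives no correlations.** The seven listed covariates use 7 degrees of freedom and by themselves leave the residual SD unchanged. The two added terms explain a share R² of the remaining variance in T4 comfort (partial R²), varied from 0 to 0.20.

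**Effect of adding two terms, 34 per arm (N = 68).**
- With q covariates, the treatment variance is multiplied by 1 + q/(N - q - 3) for expected covariate imbalance.
- For q = 7 this is 1 + 7/58 = 1.1207. For q = 9 it is 1 + 9/56 = 1.1607.
- SE ratio = sqrt[(1.1607/1.1207) × (1 - R²)].
- Power uses the noncentral t with N - 2 - q degrees of freedom: 59 before, 57 after.

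| Partial R² of the two added terms | Change in treatment SE | Power at d = 0.81 (87.3% without them) |
|---|---|---|
| 0 | +1.8% | 86.2% |
| 0.05 | -0.8% | 87.8% |
| 0.10 | -3.5% | 89.5% |
| 0.20 | -9.0% | 92.6% |

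The SE breaks even when 1 - R² = 1.1207/1.1607, so R² is about 0.035. For a single added term the break-even is about 0.02.

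**Chance imbalance.** The SD of a standardised baseline difference is sqrt(2/n): 0.224 for n = 40 and 0.243 for n = 34. The probability that it exceeds 0.3 SD in either direction is 18% and 22% respectively. If T0 anxiety correlates 0.3 to 0.5 in absolute value with T4 comfort (assumption), an imbalance of 0.3 SD moves the T4 comfort difference by 0.3 × 0.3 = 0.09 to 0.3 × 0.5 = 0.15 SD. That is 11% to 19% of 0.81.

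**If T0 comfort is also in the model.** Let a be the correlation of T0 with T4 comfort, b that of T0 anxiety with T4 comfort, and c that of T0 anxiety with T0 comfort. Then R² for both = (a² + b² - 2abc)/(1 - c²), and the partial R² of anxiety = (R² for both - a²)/(1 - a²).
- Example: a = 0.6, b = -0.4, c = -0.5 gives (0.36 + 0.16 - 0.24)/0.75 = 0.373, then (0.373 - 0.36)/0.64 = 0.021.
- Over a = 0.5 to 0.7, b = -0.3 to -0.5 and c = -0.4 to -0.6 (all assumed), anxiety adds a partial R² of about 0 to 0.14. That is an SE reduction of 0 to 7% before the charge for the extra degree of freedom.

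**The case against.** The strongest case against is that covariate choice is discretionary, that the list is introduced with open wording in a condensed article, and that every benefit figure rests on assumed correlations. That is fair as to size. It does not remove the point: the article does name a set, and the two omitted variables are closer to its definition of comfort than most of those included.

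Several further objections stand and limit the claim:

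- **No contradiction.** A reader might infer that the limitation sentence conflicts with Table 2. It does not. The sentence concerns pre-existing conditions, whereas a single 100 mm line rates anxiety on the day. At most the sentence is broader than it needs to be.
- **No bias.** A reader might take an uncorrected chance imbalance for bias. Under randomisation the unadjusted test keeps its type I error, and its standard error already covers this variation.
- **Differential response is untouched.** The limitation is about how patients respond to VR, which is effect modification. A main-effect covariate does not deal with that.
- **Not free.** Below a partial R² of about 0.035 the two terms cost a little power. If education, stage or cycle need several degrees of freedom each, the model is more crowded than assumed here.
- **Baseline comfort overlaps.** T0 SGCQ is also absent from the list and would absorb part of the gain. If change scores are compared and anxiety correlates equally with T0 and T4 comfort (equal SDs), the shift from an imbalance in anxiety cancels.
- **ECOG is weakly supported.** Eligibility restricts it to 0-2, and the definition of comfort does not mention performance status.

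**Conclusion.** The point holds as a minor improvement to the analysis. T0 anxiety and T0 pain are available for every patient before allocation is revealed, are likely to be prognostic for comfort on the article's own definition, and are missing from the named covariates. With 34 per arm and seven covariates in the model, adding both changes power at d = 0.81 from 87.3% to somewhere between 86.2% and 92.6% for a partial R² of 0 to 0.20. The result is a gain above about 0.035 and a small loss below it. These figures rest on assumed partial R² values and on one degree of freedom per listed covariate, and the gain is smaller once T0 SGCQ is in the model. The documents do not support calling this an internal contradiction, a source of bias, or a way to remove the stated limitation about response to VR.

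**What to change.** In Data analysis, name T0 VAS-A and T0 NPRS as prespecified continuous covariates in the comfort regression, alongside T0 SGCQ if that is added. ECOG is optional. Decide this before outcome data are seen.

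In the strengths and limitations box, the sentence may be narrowed to say that prior psychological conditions are not collected, while anxiety at T0 is recorded and adjusted for. It should not suggest that this adjustment deals with differential response to VR.

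The cost is about two sentences and two degrees of freedom, with no new data. The downside is a slight loss of power if the two variables turn out to explain very little.

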## Introduction

The cancer incidence in Indonesia (136.2/100 000 population) is the 8th highest in Southeast Asia and 23rd highest in Asia.^1^ According to Basic Health Surveillance (Riskesdas),^2^ the prevalence of cancer in Indonesia increased from 1.4 in 2013 to 1.49 in 2018. Of the total of 396 914 cancer cases in Indonesia in 2020, the top three most common cancer types were breast cancer (65 858 cases; 16.6%), cervical cancer (36 633 cases; 9.2%) and lung cancer (21 392 cases; 8.8%).^3^ The region with the highest prevalence of cancer is the Special Region of Yogyakarta (DIY) Province (4.86/1000 population), and 23% of the patients with cancer in this region receive chemotherapy, which is the second-most-common cancer management strategy after surgery.^2^

Patients undergoing chemotherapy experience various adverse effects.^4^ Moreover, they may experience physical and psychological discomfort caused by the treatment drugs, invasive procedures and chemotherapy environments. In general, 86% of patients with cancer experience pain, nausea, vomiting, mucositis, diarrhoea and alopecia.^5 6^ Other side effects include psychological problems, such as anxiety, feelings of hopelessness, depression, anger, fear, vulnerability and a sense of loss of control.^7^ Management of the side effects of chemotherapy by using drugs is not fully effective and may cause other side effects, which can cause further patient discomfort.^8 9^

Comfort is defined as a lack of pain, distress, worry and uneasiness, and it is one of the most crucial factors in holistic nursing care.^10 11^ Focusing on patients’ biophysiological aspects (eg, symptom management) as well as psychospiritual, environmental and sociocultural aspects related to healing is crucial for maintaining their well-being.^12^ Kolcaba explained that in addition to providing basic care to patients, nurses must provide special and unique nursing care to each patient to increase patient comfort.^13 14^ Patients with cancer require physical, social and spiritual support and a comfortable environment to have a sense of life meaning.^12 15 16^ Meeting the comfort needs of patients with cancer positively affects the patients’ satisfaction with the services they receive, their treatment adherence and their overall quality of life.^11 17^

Many non-pharmacological or alternative approaches are used in the management of chemotherapy side effects.^18^ Some studies have reported that non-pharmacological therapies, such as music therapy, acupuncture, massage, guided imagery, hypnosis, acupressure and virtual reality (VR) therapy, can alleviate physical and psychological symptoms in patients with cancer.^19 20^ However, most non-pharmacological therapies involve the use of conventional methods; few have incorporated technologies, such as VR, into alternative therapy.^21^ The use of VR in both cancer research and therapy remains limited.^22^

VR therapy is gaining popularity in complementary medicine due to its ability to overcome certain limitations of traditional therapy.^23 24^ First, VR offers an immersive and interactive environment that fosters a sense of presence and transports individuals to a different reality, potentially reducing anxiety and pain perception.^25^ Research has shown that this immersive experience can create a therapeutic effect. Second, VR therapy provides a customisable and controlled environment that can be tailored to meet the specific needs of individual patients.^26^ This personalised approach allows for a more targeted and effective treatment experience. By adapting the virtual scenarios and activities to the patient’s preferences and requirements, VR therapy offers a unique and individualised intervention. Although VR has been partially applied in cancer care, especially to reduce patient anxiety and pain during invasive procedures.^21 27^

Although scientific evidence of the effectiveness of using VR in the treatment of cancer continues to grow, findings regarding the use of smartphone-integrated VR remain limited.^28 29^ Therefore, in the present study, we proposed an innovative strategy for the management of discomfort in patients undergoing chemotherapy by using smartphone-based virtual reality relaxation (S-VR) with content including natural panoramic views and three-dimensional relaxation music. It is anticipated that this alternative therapy will help alleviate symptoms in chemotherapy patients by reducing anxiety and diverting attention from pain. However, further research is needed to explore the full potential and efficacy of smartphone-based VR therapy in managing chemotherapy-related symptoms.

The primary objective of this study is to determine the efficacy of S-VR in increasing comfort in patients with cancer undergoing chemotherapy. The secondary objectives of this study are to assess the effects of S-VR on the symptom management self-efficacy, anxiety, pain and vital signs (pulse and blood pressure) of patients with cancer undergoing chemotherapy. We hypothesise that relative to the control group, the patient group that receives the S-VR intervention will experience greater improvements in their comfort levels.

